# Comparison of the effect of three different protein content enteral diets on serum levels of proteins, nitrogen balance, and energy expenditure in critically ill infants: study protocol for a randomized controlled trial

**DOI:** 10.1186/s13063-019-3686-8

**Published:** 2019-10-11

**Keywords:** Children, Intensive care, Nutrition, Enteral feeding, Protein intake, Protein balance

## Abstract

**Background:**

Nutritional support is essential in the care of critically ill children since malnutrition in this population is associated with increased morbidity and mortality. Injury in patients admitted to pediatric intensive care units (PICU) results in a catabolic state and augmented protein breakdown, leading to a negative protein balance. Current recommendations about protein prescription in the PICU are fundamentally based on expert opinions, and the minimum threshold is 1.5 g/kg per day of protein, although protein needs could be higher in certain subgroups of patients. The main objectives of the present study are to examine whether the administration of a protein-enriched infant formula increases the serum levels of total proteins, albumin, prealbumin, transferrin, and retinol and improves nitrogen balance and to analyze the effect of the high-protein diet on energy expenditure. A secondary objective is to register possible secondary effects of the protein-enriched diet.

**Methods:**

A multicenter prospective randomized controlled trial (RCT) will be performed in three hospitals. Patients meeting inclusion criteria will be randomly allocated to one of three enteral feeding formulae with different protein contents. Blood and urine test, nitrogen balance assessment, and energy expenditure testing by indirect calorimetry will be performed at the beginning of the nutrition regimen and at 24 h, 72 h and 5–7 days after initiation. The sample size for this trial is estimated to be 90 participants (about 30 participants in each group). The data analysis will be by intention to treat.

**Discussion:**

This RCT will provide new data about the amount of protein needed to improve levels of serum protein and nitrogen balance, a surrogate of protein balance, in critically ill infants receiving enteral nutrition.

**Trial registration:**

ClinicalTrials.gov identifier: NCT03901742. Registered April 1, 2019 – Retrospectively registered.

**Electronic supplementary material:**

The online version of this article (10.1186/s13063-019-3686-8) contains supplementary material, which is available to authorized users.

## Background

Nutritional support is an essential aspect in the care for children with critical illness. Malnutrition has been reported with a prevalence of between 24% and 70% of critically ill children, depending on the series [1–5]. It can be present before admission or develop and increase during the hospital stay [6] because of several factors, such as metabolic stress response, inaccurate estimation of energy requirements, and inappropriate nutrient delivery [7]. Protein-caloric malnutrition, which has an incidence of 15–20% [8], is the most important type of malnutrition in pediatric intensive care units (PICUs). It is associated with poor outcomes in critically ill children: malnourished patients present an increased physiologic instability and quantity of care [9] and have a higher duration of mechanic ventilation and length of stay and increased mortality [2, 3, 10].

Injury in the pediatric population admitted to intensive care units results in a catabolic state and increased protein turnover. Hepatic protein synthesis is enhanced, but there is an even more augmented muscle protein breakdown, leading to negative net protein balance (PB), which conduces to a loss of lean body mass [11–13]. The progressive degradation of muscle mass can affect the diaphragm and other muscles involved in respiration, which may contribute to the onset or worsening of respiratory failure and even loss of heart muscle [14]. These changes are observable within the first two weeks of admission [6], but the most pronounced deficit of calories and proteins occurs during the first few days. Infants under the age of two are particularly susceptible because of an intrinsic lack of endogenous stores and greater baseline requirements [12].

Current recommendations about protein prescription in critically ill children are fundamentally based on expert opinions [15] since studies on protein supplementation are scarce and have small sample sizes and heterogeneous patient populations, doses of protein, and route of administration. The American Society of Enteral and Parenteral Nutrition (ASPEN) recommends, in their latest guidelines, a minimum intake of protein of 1.5 g/kg per day for children admitted to the PICU [16], a minimum threshold supported by a systematic review including 347 mechanically ventilated PICU patients [17] and a cohort study with 76 subjects [18].

Higher protein intake has been associated with early achievement of positive nitrogen balance (NB), a surrogate of PB [19–21], promoting protein anabolism [22]. Moreover, higher protein delivery has been related to lower mortality and higher ventilator-free days in PICU patients [23, 24]. However, the exact and safe amount of protein needed to avoid negative PB remains unclear. Protein intakes greater than 3 g/kg per day have been associated with elevated serum urea nitrogen levels and metabolic acidosis [19, 20, 25, 26], but other studies have reported a higher incidence of lower intelligence quotient in very-low-birth-weight infants receiving over 6 g/kg per day of protein [27, 28].

The aim of the present study is to analyze whether the administration of a high-protein diet improves protein metabolism (serum protein levels and NB) in critically ill infants without increasing energy expenditure assessed by indirect calorimetry. A secondary objective is to register possible secondary effects of the protein-enriched diet.

## Methods

### Hypothesis and aims of the study

The hypotheses of this study are that (1) critically ill infants receiving a higher amount of proteins on enteral feeding will experience a higher increase on serum protein levels—total proteins, albumin, prealbumin, transferrin, and retinol binding protein (RBP)—and NB than children receiving a standard enteral diet, (2) the administration of an enriched protein and high-protein-enriched diet does not increase energy expenditure in critically ill infants, and (3) protein-enriched and high-enriched protein enteral diets are well tolerated, and mild gastrointestinal side effects and tolerable serum urea and total protein elevation are adverse events.

The corresponding objectives are (1) to analyze whether the administration of a higher amount of protein on enteral diet improves protein metabolism observed by the increase of specific serum protein levels (total proteins, albumin, prealbumin, transferrin, and RBP) and NB in critically ill infants, (2) to evaluate the effect of protein supplementation on energy expenditure in these patients, and (3) to register possible secondary effects of the administration of protein-enriched and high-enriched protein diet.

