Continuous enteral nutrition will be typically initiated within the first 24 h of PICU admission, by a transpyloric or nasogastric tube, at a rate of 0.5–1 mL/kg per hour, with increases of 0.5–1 mL/kg every 3–4 h, if well tolerated, to reach a caloric intake of 60–65 kcal/kg per day or as needed on the basis of resting energy expenditure measured by indirect calorimetry. There is no limit of time before the patient must be recruited as long as it is before the enteral feeding is initiated. The establishment of enteral nutrition should never be delayed by achieving enrollment.

Demographic data—gender, age, weight, height, and diagnosis on admission—will be recorded at inclusion. The risk of mortality at admission will be calculated by using pediatric scales: Pediatric Index of Mortality 2 (PIM2), Pediatric Risk of Mortality (PRISM), and Pediatric Logistic Organ Dysfunction (PELOD).

Blood concentrations of urea, creatinine, total proteins, albumin, prealbumin, transferrin, RBP levels, urinary concentration of urea in 24 h or isolated urine sample, and energy expenditure, oxygen consumption (VO_2_), and carbon dioxide production (VCO_2_) by indirect calorimetry (Datex S5 monitor, E-COVX; GE Healthcare/Datex-Ohmeda, Helsinki, Finland) will be measured at admission and at days 1, 3, and 5–7 after initiation of enteral feeding. Air leaks will be measured by using the mechanical ventilator. Calorimetry-derived data will be collected only in patients who meet all the following requirements: tracheal intubation, air leakage less than 10 %, fraction of inspired oxygen (FiO2) less than 80%, not treated with inhaled medicinal gases (nitric oxide, sevofluorane or heliox), and not connected to extracorporeal membrane oxygenation (ECMO). The collection of indirect calorimetry data will be carried out over 30 to 120 min.

NB will be calculated as nitrogen intake minus total nitrogen losses. Total nitrogen losses will include total urinary nitrogen and fecal/miscellaneous losses estimated in accordance with the World Health Organization recommendations [29]. Other blood biochemical parameters such as glucose, cholesterol, triglycerides, procalcitonin, C-reactive protein, ions, and blood gas will also be recorded.

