### Study outcomes

The primary outcome of the study will be the variation of NB from baseline to the study ending and the incidence of hyperproteinemia or uremia causing the need to stop the study. Secondary outcomes include the variation of plasma protein levels (total proteins, albumin, prealbumin, transferrin, and RBP), expenditure energy measured by indirect calorimetry, and the incidence of gastrointestinal complications (abdominal distension, vomiting, diarrhea, and excessive gastric residue) and metabolic acidosis.

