### Statistical analysis

As there are no previous studies reporting expected standard deviations, we use the standardized difference of means for computing the optimal minimum number of patients to include in the trial. The calculation of the sample size was carried out with EPIDAT 3.1 software. Given a significance level of 5% (type I error), a power of 80% (complementary of the type II error), and a minimum detectable standardized difference of means of 0.9, we need 30 patients per group (Bonferroni correction included).

We will use an intention-to-treat approach. A descriptive analysis will be performed where quantitative variables will be described by their means and standard deviations or their medians and interquartile ranges, as appropriate. The quantitative ones will be summarized by their absolute and relative frequencies. Parametric and non-parametric tests will be employed for contrasting equality among groups.

Univariate and multivariate mixed models will be used in order to assess the effects size of the different diets (fixed effects) on the patients (random effects) unadjusted and adjusted by potential confounders, respectively. *P* values under 5% will be considered statistically significant.

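### The protocol claims that enriched diets do not raise energy expenditure, but its stated analysis contains no rule by which a no-increase conclusion could be supported

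*Protocol article*

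**What the plan says.** In the protocol article, Hypothesis and aims of the study, hypothesis 2 is that "the administration of an enriched protein and high-protein-enriched diet does not increase energy expenditure in critically ill infants". The aim at the end of the Background is to improve protein metabolism "without increasing energy expenditure assessed by indirect calorimetry". The matching objective 2 is neutral: "to evaluate the effect of protein supplementation on energy expenditure in these patients". Study outcomes lists "expenditure energy measured by indirect calorimetry" as a secondary outcome, although the Abstract counts the effect on energy expenditure among the main objectives.

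Under Recruitment, randomization, and study development: "Calorimetry-derived data will be collected only in patients who meet all the following requirements: tracheal intubation". The further conditions are air leak below 10%, FiO2 below 80%, no inhaled medicinal gases and no ECMO. Measurements are planned at admission and at days 1, 3 and 5–7.

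Statistical analysis states that "Parametric and non-parametric tests will be employed for contrasting equality among groups", that "Univariate and multivariate mixed models will be used in order to assess the effects size of the different diets", and that P "values under 5% will be considered statistically significant". The sample size is 30 per group for a standardized difference of 0.9.

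**The concern.** Hypothesis 2 asserts the absence of an effect, whereas an equality test can only provide evidence that an effect is present. The mixed models will estimate the effect, but nothing says how small an estimate, or how low its upper confidence limit, would have to be before the no-increase claim is supported. Short of a significant fall in expenditure, the only result under the stated rule that sits comfortably with hypothesis 2 is a non-significant one. That result becomes more likely as fewer infants are measured, so weak data would favour the hypothesis.

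There is also a mismatch of population. Hypothesis 2 speaks of critically ill infants, and the inclusion criteria do not require intubation, yet energy expenditure is observed only in intubated infants who meet the calorimetry conditions.

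At stake is half of the stated aim. The Discussion says that the results will inform whether an enriched diet is useful, and a no-increase statement resting on a non-significant test could be carried into that judgement.

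**Working it through.** **Inputs from the protocol article.** 30 per group, standardized difference 0.9, significance level 5%, power 80%, Bonferroni correction included (Statistical analysis). Three diet groups. Energy expenditure only in infants meeting the calorimetry conditions.

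**Assumptions, not in the document.** Two-sided testing. Evaluable infants per arm: 30 as the most favourable case, then 18 and 12 (60% and 40% of 30) to show the range. A true increase of 0.5 SD as an illustration. Three pairwise comparisons for the Bonferroni correction.

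**1. The plan's own figure.** n per group = 2(z₁₋α/₂ₖ + z₀.₈)² / 0.9². With k = 3: 2(2.394 + 0.842)² / 0.81 = 25.8, so 26; the t-based version gives 28. With k = 6 the normal formula gives 30. The stated 30 is therefore close to what a calculation for detecting a difference yields. It is not a calculation for excluding an increase, and it is not tied to energy expenditure or to the calorimetry subset.

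**2. Precision of one enriched-versus-standard comparison at one visit, unadjusted.** Half-width of the 95% interval in SD units = t₀.₉₇₅,₂ₙ₋₂ × √(2/n).

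- n = 30: 2.002 × 0.258 = 0.52
- n = 18: 2.032 × 0.333 = 0.68
- n = 12: 2.074 × 0.408 = 0.85

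At n = 30, an observed difference of exactly zero leaves an upper limit of 0.52 SD. An observed increase just short of significance leaves one of about 2 × 0.52 = 1.04 SD.

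**3. Chance of detecting a true 0.5 SD increase** (two-sided 5%, noncentral t, noncentrality 0.5/√(2/n)).

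- n = 30: noncentrality 1.94, power 48%
- n = 18: noncentrality 1.50, power 31%
- n = 12: noncentrality 1.22, power 22%

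Such an increase would be non-significant in about 52%, 69% and 78% of trials.

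**4. Effect of baseline adjustment.** Adjusting for the admission value multiplies the half-width by √(1 − r²). For an assumed correlation r of 0.5 to 0.7 at n = 30, the half-width becomes 0.52 × 0.866 = 0.45 down to 0.52 × 0.714 = 0.37 SD, and power for 0.5 SD rises to 59–76%. The imprecision shrinks but remains.

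**5. What a formal margin would demand.** To exclude an increase of 0.5 SD (again only an illustration) at one-sided 2.5% with 80% power and a true difference of zero: n = 2(1.960 + 0.842)² / 0.5² = 62.8, so 63 evaluable per arm. With 30 evaluable the power is 49%; with 12 it is 23%.

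**The case against.** The strongest reply is that the protocol is not confined to significance tests. It plans mixed models for effect size, unadjusted and adjusted, and objective 2 is already worded as evaluating an effect. Energy expenditure is a secondary outcome, and a margin or reporting rule for it could sit in an analysis plan that is not shown. All of this is fair. It makes the remedy easy and lowers the weight of the point. It does not remove the conflict, because hypothesis 2 and the Background aim go further than objective 2, and nothing stated connects the estimate to the no-increase claim. The point concerns a mismatch between things the article does state, not an omitted detail.

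A reader might infer three stronger things that the document does not support:

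- **That the investigators will take a non-significant result as proof of no increase.** No sentence says so; it is a risk that the wording leaves open.
- **That fewer than 30 per arm will be measured.** The eligible share is not given, so subset sizes are assumptions.
- **That the later visits describe only the sickest infants.** No extubation rate is given, and the exclusions for high FiO2, inhaled gases and ECMO remove some of the most severely ill.

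The power figures are also for an unadjusted single-visit comparison, not for the planned mixed model, and the 0.5 SD has no source in the protocol.

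**Conclusion.** The point holds as a mismatch between claim and analysis. Hypothesis 2 and the Background aim assert no increase in energy expenditure, and the stated tests, effect sizes and 5% threshold provide no route to that conclusion. In the most favourable case for numbers, 30 evaluable per arm, a non-significant unadjusted comparison is compatible with increases of 0.52 SD or more and would miss a true 0.5 SD increase about half the time. With assumed baseline correlations of 0.5 to 0.7, the half-width is still 0.37 to 0.45 SD. Whether increases of this size matter clinically is for the investigators to say. Separately, any conclusion applies only to intubated infants who meet the calorimetry conditions. The design, randomization and primary outcome are not affected.

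**What to change.** - Reword hypothesis 2 and the Background aim as an estimation objective, in line with objective 2.
- Report the mixed-model differences for both enriched diets, PEN minus SEN and HPEN minus SEN, each with a 95% confidence interval.
- State that P above 5% will not be taken as evidence of no increase.
- Limit the conclusion to intubated infants meeting the calorimetry criteria, and report the number measured per arm and visit.
- Draw a conclusion of no relevant increase only if the investigators fix a margin before any energy-expenditure data are analysed and the upper confidence limit lies below it. The margin is a clinical choice, and none is proposed here.

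The estimation route costs only wording and two intervals, with no extra patients or measurements; the downside is a weaker claim about energy expenditure. The margin route is an option, not a requirement. With 30 or fewer evaluable per arm it would probably be underpowered unless the agreed margin is wide.

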### Study design

This is an open randomized controlled clinical trial. The study was conceived and designed in 2010. It has been retrospectively registered on the Clinical Trials Database (ClinicalTrials.gov) with the registry number NCT03901742. This protocol, version 1.0, was approved on September 30, 2010. Central ethical approval has been confirmed from the institutional review board of Hospital General Universitario Gregorio Marañón (reference approval number 2010–022851-47), and recruiting will not begin at other centers in the trial until local ethical approval has been obtained. Informed consent will be obtained from parents before their children are enrolled in the study. A report releasing study results will be submitted for publication in an appropriate journal. This protocol has been written in accordance with the Standard Protocol Items: Recommendations for Interventional Trials (SPIRIT) (Fig. 1). The study flowchart is shown in Fig. 2. A SPIRIT checklist is provided in Additional file 1.

**Fig. 1 Fig1:**
[figure not shown]
Standard Protocol Items: Recommendations for Interventional Trials (SPIRIT) diagram for this protocol

**Fig. 2 Fig2:**
[figure not shown]
Flowchart for this protocol, comparing the effect over protein metabolism of three different amounts of protein delivery. *Abbreviations*: *EN* enteral nutrition, *NB* nitrogen balance, *PICU* pediatric intensive care unit.

### Study setting

PICUs from three hospitals in Spain will participate: Hospital General Universitario Gregorio Marañón (Madrid), Hospital Clínico Universitario de Santiago (Santiago de Compostela), and Hospital Universitario Central de Asturias (Oviedo).

### Participants

#### Inclusion criteria

The following are the inclusion criteria:
children 1 month to 2 years oldchildren admitted to the PICUchildren receiving enteral nutrition with an estimated length of over 72 h.

#### Exclusion criteria

Children who met any of the following criteria will be excluded:
age less than 1 month or more than 2 yearsdiabetes mellitus or any inborn metabolic errorparenteral nutritionbicarbonate infusionrenal replacement therapychildren receiving exclusive breastfeeding or in need of special enteral formula.

### Recruitment, randomization, and study development

Once an eligible patient is admitted to the PICU, written informed consent will be requested from parents or legal representative of the child by the physician responsible for the patient. They will be made aware that participation is voluntary, and they will be allowed to refuse further participation in the trial whenever they want.

After enrollment, the patient will be allocated randomly, in order of recruitment, into one of the three diet groups by using a randomized data table generated with EPIDAT 3.1 software (Servicio de Información sobre Saúde Pública de la Dirección Xeral de Saúde Pública de la Consellería de Sanidade, Xunta de Galicia, in collaboration with the Health Information and Analysis Unit of the Pan American Health Organization (PAHO-WHO)). A copy of the randomization list will be securely stored in an envelope located in a PICU working area desk drawer, which will be opened after patient enrollment in the study. Physicians, care givers, and investigators will know the allocation prior to the start of enteral feeding.

All patients will receive exclusively enteral nutrition via a nasogastric or transpyloric tube. The Standard Enteral Nutrition (SEN) group will be fed exclusively with cow’s milk–based infant formula (Nidina 1; Nestlé, Barcelona, Spain). The Protein-enriched Enteral Nutrition (PEN) group will be fed exclusively with a polymeric infant formula (Infatrini; Nutricia, Madrid, Spain). The High Protein-enriched Enteral Nutrition (HPEN) group will receive a polymeric infant formula (Infatrini; Nutricia) supplemented with 2.6 g of protein/100 mL of formula. The source of the protein supplement will be a non-hydrolyzed protein cow’s milk–based formula (Resource Protein Instant; Nestlé) (Table 1).

**Table 1 Tab1:** Composition of diets used in the study

	Protein (g)	Carbohydrate (g)	Lipids (g)	Energy (kcal)
Standard enteral nutrition	1.7	7.4	3.4	67
Protein-enriched enteral nutrition	2.6	10.3	5.4	100
High protein-enriched enteral nutrition	5.1	10.5	5.5	110

Content per 100 mL

Since this is an open-label trial, the assigned diet will be written down on the medical prescription of each patient and will be prepared by the PICU staff at their own unit, using for it the branded bottles where the different formulae are commercialized.

Continuous enteral nutrition will be typically initiated within the first 24 h of PICU admission, by a transpyloric or nasogastric tube, at a rate of 0.5–1 mL/kg per hour, with increases of 0.5–1 mL/kg every 3–4 h, if well tolerated, to reach a caloric intake of 60–65 kcal/kg per day or as needed on the basis of resting energy expenditure measured by indirect calorimetry. There is no limit of time before the patient must be recruited as long as it is before the enteral feeding is initiated. The establishment of enteral nutrition should never be delayed by achieving enrollment.

Demographic data—gender, age, weight, height, and diagnosis on admission—will be recorded at inclusion. The risk of mortality at admission will be calculated by using pediatric scales: Pediatric Index of Mortality 2 (PIM2), Pediatric Risk of Mortality (PRISM), and Pediatric Logistic Organ Dysfunction (PELOD).

Blood concentrations of urea, creatinine, total proteins, albumin, prealbumin, transferrin, RBP levels, urinary concentration of urea in 24 h or isolated urine sample, and energy expenditure, oxygen consumption (VO_2_), and carbon dioxide production (VCO_2_) by indirect calorimetry (Datex S5 monitor, E-COVX; GE Healthcare/Datex-Ohmeda, Helsinki, Finland) will be measured at admission and at days 1, 3, and 5–7 after initiation of enteral feeding. Air leaks will be measured by using the mechanical ventilator. Calorimetry-derived data will be collected only in patients who meet all the following requirements: tracheal intubation, air leakage less than 10 %, fraction of inspired oxygen (FiO2) less than 80%, not treated with inhaled medicinal gases (nitric oxide, sevofluorane or heliox), and not connected to extracorporeal membrane oxygenation (ECMO). The collection of indirect calorimetry data will be carried out over 30 to 120 min.

NB will be calculated as nitrogen intake minus total nitrogen losses. Total nitrogen losses will include total urinary nitrogen and fecal/miscellaneous losses estimated in accordance with the World Health Organization recommendations [29]. Other blood biochemical parameters such as glucose, cholesterol, triglycerides, procalcitonin, C-reactive protein, ions, and blood gas will also be recorded.

Time between PICU admission and the initiation of enteral nutrition, total daily enteral energy and protein delivery, intravenous albumin infused, and other treatments such as vasoactive drugs, neuromuscular blockers, sedatives and analgesic drugs, diuretics, and steroids will be registered.

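### The randomization list itself is kept in an envelope in the PICU, so as written only the first allocation from each copy is concealed from the staff who recruit

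*Protocol article*

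**What the plan says.** All the relevant statements are in the protocol article, mostly under *Recruitment, randomization, and study development*.

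- Sequence: "the patient will be allocated randomly, in order of recruitment, into one of the three diet groups by using a randomized data table".
- Storage: "A copy of the randomization list will be securely stored in an envelope located in a PICU working area desk drawer".
- Opening: the envelope is one "which will be opened after patient enrollment in the study".
- Recruitment: consent is requested "by the physician responsible for the patient".
- Timing: "There is no limit of time before the patient must be recruited as long as it is before the enteral feeding is initiated". The sentence that follows adds that enrolment must never hold up the start of feeding.

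Under *Study setting*, "PICUs from three hospitals in Spain will participate". The abstract gives a total of 90 infants, about 30 per group. The article does not say whether there is one list or one per centre.

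**The concern.** Randomisation protects a comparison only if the person deciding whether an infant enters the trial cannot know which arm comes next. Here the stored object is the list, not a set of single assignments. It is kept where the recruiting physicians work, and it must be opened to allocate the first infant. From then on, the entries for later infants can be read before those infants are enrolled.

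What is at stake is the comparability of the three diet groups. Under *Study outcomes*, the primary outcome combines the change in nitrogen balance with the occurrence of hyperproteinemia or uremia that ends the study. Both may depend on the metabolic state of the infants who enter each arm. If enrolment decisions are made with the next arm known, differences between groups may partly reflect who was enrolled and not which diet was given.

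**Working it through.** The check is mainly one of reading the stated procedure through, with a simple count.

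**1. What each step of the procedure reveals.**
- Before the first infant is enrolled, the envelope is closed, so the first entry is concealed.
- After the first infant is enrolled, the envelope is opened and the list is read. The article describes no resealing, no one-allocation envelopes and no independent holder.
- For the second and later infants, entries are taken in sequence from a list that has already been opened. The rule that opening follows enrolment was satisfied by the first infant and conceals nothing further.

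**2. How many allocations are exposed.** Inputs: 90 infants (abstract; 3 × 30 = 90) and 3 centres (*Study setting*).
- One list for the whole trial: 90 − 1 = 89 of 90.
- One list per centre, each centre enrolling at least one infant: 90 − 3 = 87 of 90.

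Both are ceilings. They count entries that could be read in advance by someone with access to the drawer, not entries known to have been read.

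**3. What exposure means for one enrolment decision.** With the list open, the next arm is known with probability 1. Under concealed simple allocation in equal proportions to three arms, it could be guessed with probability 1/3. (Simple equal allocation is an assumption for this comparison; the article does not describe blocking.)

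**4. Whether staff have room to act on it.** Eligibility includes matters of judgement: whether enteral feeding is expected to last more than 72 hours (*Inclusion criteria*) and whether a special formula is needed (*Exclusion criteria*). Whether to approach a family is also in the physician's hands. The arms differ in a way staff may care about: Table 1 gives 1.7, 2.6 and 5.1 g of protein per 100 mL, and *Study ending* makes raised urea or total protein a reason to stop. That is a possible motive, not evidence of steering.

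**5. Link to the sample size.** None. The stated 30 per group is not in dispute. A two-sided t-test at 0.05/3, with a standardized difference of 0.9 and 80% power, needs 28 per group (three pairwise comparisons assumed), close to the plan's figure.

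**The case against.** The strongest defence is that the text shows an intent to conceal: the list is described as securely stored and is to be opened only once a patient is enrolled. The article may also condense a fuller procedure. Both points are fair. But the point does not rest on missing detail. What is stated, a list in an envelope used in sequence and opened at enrolment, conceals only the first entry of each copy. That all later entries become visible is an inference from this wording, though a strong one.

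Several stronger readings are tempting and should be set aside.

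- **That recruiters can time enrolment to get the arm they want.** The absence of a recruitment deadline might suggest this. But feeding typically starts within 24 hours of admission and may not be delayed for enrolment. The list also advances only when another infant is enrolled. From 28 December 2016 to the end of December 2020 is about 1,464 days, and 1,464 / 90 is about 16 days per enrolment across all centres. Waiting for someone else to take an unwanted slot is rarely feasible. The realistic route is not enrolling an infant.
- **That the open label is itself the defect.** The article says "Physicians, care givers, and investigators will know the allocation prior to the start of enteral feeding". That describes knowledge of an infant's own assignment after enrolment. An open-label trial can still conceal the next allocation, so this sentence is not evidence for the point.
- **That one drawer cannot serve three hospitals.** How the other centres obtain allocations is operational detail that an article may leave to the full protocol.
- **That the bias can be expressed in standard deviations.** A shift of 0.2 to 0.3 SD would be 0.2/0.9 = 22% to 0.3/0.9 = 33% of the design difference, but nothing in the article supports such a shift.

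It is also true that nitrogen balance is analysed as a change from baseline, that PIM2, PRISM and PELOD are recorded, and that adjusted mixed models are planned (*Statistical analysis*). These can reduce imbalance in what is measured. They cannot correct for a clinical impression that influenced enrolment but was not recorded.

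**Conclusion.** The concern holds as a defect of allocation concealment. As written, the procedure exposes up to 89 of 90 allocations (one list) or 87 of 90 (one list per centre) to the staff who judge eligibility and seek consent. They could decide whether to enrol an infant knowing the next arm, and the planned adjustment could not fully remove the resulting selection bias.

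The conclusion assumes that the envelope holds the list as described and is not replaced by a fuller concealed procedure elsewhere. A reader might infer that infants were steered between arms, or that the results carry a bias of known size. The article supports neither: nothing shows that steering occurred, and the size of any bias cannot be derived from it. The point still deserves action, because concealment cannot be restored at the analysis stage.

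**What to change.** Remove the list from the PICU. For all remaining infants, reveal one allocation at a time by either of two routes:

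- central allocation by telephone or web; or
- sequentially numbered, opaque, sealed envelopes holding one allocation each, prepared by someone who does not recruit.

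In both cases, release the allocation only after eligibility and consent are recorded. Do not make release wait for all baseline measurements: these may include a 24-hour urine collection and 30 to 120 minutes of calorimetry, and waiting could conflict with the article's own rule that enrolment must not delay feeding.

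Report how infants were allocated before the change as a limitation, with a descriptive comparison of those randomised before and after. This comparison should not be treated as a test of bias. Recruitment began in December 2016 and the article is dated October 2019, so the later group may be small (its size is not given), and the comparison is confounded with calendar time.

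The cost is a short amendment and minor preparation work, with no extra patients or procedures.
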